### **Study Design**

**The scientific integrity of the study and the credibility of the study data depend substantially on the study design and methodology. The design of the study should include information on the type of study, the research population or the sampling frame, and who can take part (e.g. inclusion and exclusion criteria, withdrawal criteria etc.), and the expected duration of the study**

**(The same study can be described in several ways, and as complete a description of the study as possible should be provided. For example, a study may be described as being a basic science research, epidemiologic or social science research, it may also be described as observational or interventional; if observational, it may be either descriptive**

**or analytic, if analytic it could either be cross-sectional or longitudinal etc. If experimental, it may be described as a controlled or a non controlled study. The link below provides more information on how to describe a research study**

The human controlled intervention study is conducted according to the guidelines laid down in the declaration of Helsinki, and was approved by the Ethical Committee of the Ghent University Hospital (B670201630414). Participants, members of the research group and familiars, are contacted providing an invitation letter and can register for the study within two weeks after the call. All participants have to sign an informed consent. Each participant is informed on his/her right to withdraw from the study at any time and to consult a doctor immediately and inform us if they fell not right during the study but no adverse event are reported for any volunteers. Besides, no medical examinations or interventions are carried out in this study. The study is performed with 20 volunteers throughout an intervention and longitudinal trail, and recruited in Flanders (Belgium). All people older than 18 years old can take part in the study, less pregnant or breast-feeding women due to the potential risk to both mother and foetuses and persons with severe problems with liver, bile or kidney due to related risks for interferences with the mycotoxin metabolism. The volunteers are instructed to file a socio-demographic questionnaire involving details on age, gender, length, body weight, smoking, diseases, drugs or supplements, pregnancy, breast-feeding, diet and daily coffee consumption.

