The subjects have to follow a strict cereal-free diet during 3 days (Figure 1). Cereal-based foods and foods containing possible traces of wheat, rye, oats, maize and rice are restricted (*i.e.* bread and bread-based products, breakfast cereals, oat meal, muesli, cereal bars, waffles, cakes, (un)pealed rice, polenta, pizza, tortilla, pasta, popcorn, cereal-based chips, maize, beer, wine, pan meal and sauce-binders). The subjects are asked to detail their daily food intake through a questionnaire. On the third day in the morning, the subjects receive an oral bolus of DON or DON-3-glucoside based on the TDI ( $1\text{ }\mu\text{g/kg}$  body weight) and their body weight. The volunteers did the study twice: 1) DON administration and 2) DON-3-glucoside administration, between the two mycotoxin administration there are a washout period of two months. In addition, a control group of 4 volunteers follow the same protocol, however do not receive a bolus of DON or DON-3-glucoside after the cereal-free diet.

At day 3, volunteers have to collect a urine sample before the administration of the DON or DON-3-glucoside bolus (Figure 1). From the moment of administration, the 24-hours urine sample collection is requested. We deliver to each volunteer 12 containers (1L) to collect the urine. For every sampling point, time (hour of urine collection) and voided volume is recorded. All samples will be individually aliquotted to 20 mL, and stored in the freezer at  $-20^{\circ}\text{C}$  upon analysis. The samples are analysed with a Waters Acquity UPLC system coupled to a Quattro XEVO TQS mass spectrometer (Waters, Manchester, UK) was used to analyse the urine samples. Data acquisition and processing is performed with MassLynx™ version 4.1 and

QuanLynx® version 4.1 software (Waters, Manchester, UK). A Waters Acquity UPLC® HSS T3 (2.1 x 100 mm, 1.8 µm) column is applied (Waters, Manchester, UK).

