Volunteers have to be three days without eating cereals. It is difficult to control their diet for 24 h, so we absolutely trust in their free cereals diet. However, we know that if some volunteers do not follow the diet we will detect DON levels in the “blank” urine (the urine before toxin administration) and they have to repeat the intervention study. So, although we do not control totally the volunteers diet we have the “blank” urine as control of their good diet following. We deliver a list with the allowed and not allowed food to clarify even more the restricted food to the volunteers (Figure 2). On the other hand, we add four volunteers which will not take toxin administration but they do not know they are not taking the toxin administration just water. The 4 control volunteers will provide us information to compare the results. The control volunteers are random selected from the 20 volunteers. 2 males and 2 females will be randomly selected for control.

The volunteers have to answer a questionnaire where we ask for factors that could affect the toxin excretion (Figure 3). Moreover, we ask again about pregnant or breast feeding people as well as

kidney, liver or bile problems to be sure again that pregnant or breast feeding women and people with kidney, liver or bile problems are not included in the study.

Stickers with the code for each sample will be delivered to the volunteers with the urine collection containers. The volunteers have to stick each code to the urine sample and they have to add the hour of urine collection for each sample. This process is explained in detail to each volunteer when they come to collect the containers, moreover, we supply a completely detailed procedure about how to take the samples, where we added a phone number contact to call in case of doubts during the study.

Once, we received the samples from each volunteer we introduced the code, the hour and the volume for each sample in excel file and we take two aliquots of 20 mL for each samples and we stored until analysis in the freezer at -20 °C.

Then, the samples are analysed by LC-MS/MS with a previously validated method.

A flow diagram with timing assessments has been made with the study design and procedures (Figure 4).

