## Socio-demographic questionnaire

### Notes and instructions on completing the questionnaire:

This short questionnaire assesses some global affairs. We need this information to determine the results to interpret correctly. The information we collect in this questionnaire are only at for the purpose of scientific research into the metabolism and excretion of deoxynivalenol and its glucoside in humans and will be treated confidentially. This means that only the research team which is concerned with the study access to information and should not be passed to third person.

Moreover, everything is encrypted and you never mention your name. Please fill in this questionnaire them to bring along with your urine samples and give it away to one of our employees on a pre-arranged time.

Id number: .....

What is your date of birth? .....

What is your gender?

☐ Male

☐ Female

What is your height? .....cm

What is your weight? .....kg

Do you smoke cigarettes, cigars or a pipe?

☐ Yes

☐ No

Do you have a disease relating to ...?

- ☐ Liver
- ☐ Kidney
- ☐ Bile

What drugs and / or supplements you have taken the past month? What dose?

| Drugs / supplements | Doses |
|---------------------|-------|
|                     |       |
|                     |       |
|                     |       |
|                     |       |
|                     |       |
|                     |       |
|                     |       |
|                     |       |
|                     |       |
|                     |       |
|                     |       |

Are you pregnant or is there a chance that you are pregnant?

- ☐ Yes
- ☐ No

Breast-feeding?

- ☐ Yes
- ☐ No

Currently follow a diet where some foods should not be eaten because it of illness, allergy or for no reason?

- ☐ Gluten free
- ☐ Slimming free
- ☐ Diabetes
- ☐ Low salt
- ☐ Other.....

What diet do you follow?

- ☐ Western European
- ☐ Mediterranean
- ☐ Eastern
- ☐ Halal
- ☐ Kosher
- ☐ Low meat
- ☐ Vegetarian
- ☐ Vegan
- ☐ Other .....

Do you drink coffee every day? If so, how much?

- ☐ No
- ☐ Yes, I drink ..... cups of coffee per day.

Figure 4. Flow diagram with the timing assessments.

[figure not shown]

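### The protocol states no eligibility check before the second toxin bolus, and the questionnaire meant to confirm eligibility is handed in after dosing

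*Protocol*

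**What the plan says.** Study Design in the protocol admits adults, "less pregnant or breast-feeding women due to the potential risk to both mother and foetuses", and also bars "persons with severe problems with liver, bile or kidney" because these could interfere with metabolism of the toxin. The same section sets out two dosing occasions: "The volunteers did the study twice: 1) DON administration and 2) DON-3-glucoside administration", and "between the two mycotoxin administration there are a washout period of two months".

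Methodology describes how the exclusions are confirmed after recruitment. The questionnaire is given this task: "Moreover, we ask again about pregnant or breast feeding people as well as", continuing "kidney, liver or bile problems to be sure again that pregnant or breast feeding women" and people with those conditions are kept out of the study.

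The questionnaire itself (Figure 3) asks about current or possible pregnancy, breast-feeding, and liver, kidney or bile disease. Its instructions read: "Please fill in this questionnaire them to bring along with your urine samples". Study Design and Safety Considerations both say that no medical examinations are carried out, so eligibility depends on what the volunteer reports.

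**The concern.** Pregnancy, breast-feeding and organ disease can all change within two months. An exclusion justified by risk to mother and foetus has to hold at each toxin administration, not only at entry. The text ties neither the recruitment question nor the questionnaire to the second bolus. The questionnaire also reaches the team at a point where it cannot act as a screen.

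What is at stake is mainly participant safety: the protocol's own exclusion could apply to a volunteer at the second bolus with no stated step that would reveal it. A new liver, kidney or bile problem would also bear on the excretion data of that period, since the protocol itself gives interference with metabolism as the reason for excluding it.

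**Working it through.** The plan gives no figure on this point to reproduce. The check is one of timing, followed by an illustration on assumed inputs.

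**Inputs from the protocol**
- Two boluses two months apart (Study Design).
- Urine collected for 24 hours from administration (Study Design; Urine Collection).
- Form handed in with the urine samples (Figure 3 instructions).
- Eligibility asked at recruitment, then again on the form (Study Design; Methodology).
- No medical examination (Study Design; Safety Considerations).

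**When could the team learn of a change during the washout?** Take the first bolus as time 0 and the second as about 2 months.

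| Reading of the protocol | Team receives the form | Use for the second bolus |
|---|---|---|
| Form completed once, in the first period | about 1 day or more after the first bolus | Predates nearly all of the washout, so cannot show a change in it |
| Form completed in each period | about 1 day or more after the second bolus | Shows the change, but after dosing |

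Under neither reading does the team hold washout-period answers before the second bolus. Under both, the form also arrives too late to screen for the first bolus, which conflicts with the purpose Methodology gives it.

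**Illustrative size.** Assumptions, none from the protocol: k women who could conceive, annual conception rate r, constant risk, and two months as one sixth of a year.

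P(at least one conception) = 1 − (1 − r/6)^k

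| r | k = 6 | k = 8 | k = 10 |
|---|---|---|---|
| 0.05 | 0.049 | 0.065 | 0.080 |
| 0.10 | 0.096 | 0.126 | 0.155 |

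With 8 to 10 dosed women the range is about 6% to 15%. Two of the four controls, drawn from the 20 volunteers, are women who receive only water (Methodology). If the 8 to 10 include them, 6 to 8 are dosed and the range is about 5% to 13%.

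**Other items on the form**
- The drug and supplement question looks back one month ("What drugs and / or supplements you have taken the past month? What dose"). A first-period answer would therefore cover none of the two-month washout. Drug use, however, is neither an exclusion nor a regression covariate.
- The covariates are age, gender, BMI and coffee. Gender is fixed and age moves by 2/12 = 0.17 year, so only BMI and coffee could date. For an assumed 70 kg volunteer, a change of 1 to 3 kg is 1/70 = 1.4% to 3/70 = 4.3% in weight and BMI.

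**The case against.** The strongest reply is that the protocol is silent here rather than wrong. One printed form does not mean one completion: it travels with the urine samples, and urine is collected in both periods, so a repeat is a natural reading. The figures that carry the study scheme and timing are not shown, and other pages were removed before review, so a check could appear there. Study Design says who may take part without limiting this to the first bolus, so knowingly dosing an excluded volunteer in the second period would breach the protocol. Volunteers may also withdraw at any time and are asked to report feeling unwell.

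Much of this stands. A single completion cannot be asserted, and a check in an unseen figure cannot be ruled out. But a repeated form does not close the gap, because it would still be handed in after the second bolus. A volunteer might fill it in earlier and withdraw on her own account, but the team would not have reviewed it. The general instruction to report feeling unwell does not ask about a new pregnancy or diagnosis.

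Three stronger inferences are tempting and not supported:
- That an ineligible volunteer will be dosed. The text supports only that no stated step would detect the change in time.
- That new medication makes a volunteer ineligible. The protocol has no such exclusion.
- That second-period covariates are stale enough to distort results. Only BMI and coffee could change, the coffee item asks about a daily habit, and two months is short.

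The conception range is also open to challenge. Every input is assumed, and a repeated self-report would miss a pregnancy not yet recognised, so the range is not the number of cases that the fix would prevent.

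**Conclusion.** The point holds as a gap in applying the protocol's own exclusions at the second administration, together with a conflict between Methodology, which uses the questionnaire to keep ineligible people out, and the form's instructions, which have it returned after dosing. The conclusion needs only the stated timings and does not depend on how often the form is completed. It does depend on the hand-in wording being followed and on no check being stated in the figures and pages not available here.

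Its size cannot be derived from the documents. The illustrative chance of at least one conception in the washout, about 5% to 15% over the assumed inputs, shows only that the event is not negligible in a group this small. No material effect on the regression results is claimed. The change is worth making because the stake is participant safety and the cost is close to nil.

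**What to change.** Reconcile Methodology with the questionnaire's instructions. State that the existing pregnancy, breast-feeding and liver, kidney and bile items are answered by the volunteer and reviewed by the team before each administration, including the second, with the protocol's existing exclusions applied. Add a period and a completion date to the form, and record the answers by period in the Excel file. The rest of the form can still come in with the urine samples.

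The cost is one repeated page per volunteer and a few extra columns. The downside is that a volunteer found ineligible during the washout is lost from the second period. No new procedure or clinical rule is needed.

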Figure 2. List with the allowed and not allowed food during the intervention diet. The list is delivered to the volunteers to be better informed about the diet to follow during the study. Moreover, we added some diet recommendations to be followed during the days of restriction diet.

| Restricted food                                                                                                                                                                                                        | Permitted food                                                                                                                                                           |
|------------------------------------------------------------------------------------------------------------------------------------------------------------------------------------------------------------------------|--------------------------------------------------------------------------------------------------------------------------------------------------------------------------|
| 
 
• Pasta
 
• Breads or similar (small toasts, sliced bread...)
 
• Baking products (cookies, muffins...)
 
• Breakfast cereals
 
• Snacks
 
 | 
 
• Fruit
 
• Vegetable
 
• Meat
 
• Fish
 
• Nuts
 
• Dairy products
 
• Eggs
 
 |
| Beverages                                                                                                                                                                                                              |                                                                                                                                                                          |
| 
 
• Beer
 
                                                                                                                                                               | 
 
• Other
 
                                                                                                                |

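### The food list given to volunteers is narrower than the protocol's diet restriction and contradicts it on wine, so dietary DON could enter the 24-hour collection undetected

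*Protocol*

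**What the plan says.** The Project summary and the Study Design section set the same rule for the three diet days: "Cereal-based foods and foods containing possible traces of wheat, rye, oats, maize and rice are restricted". Named examples follow, ending with "polenta, pizza, tortilla, pasta, popcorn, cereal-based chips, maize, beer, wine, pan meal and sauce-binders".

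The Methodology section describes what the volunteers receive: "We deliver a list with the allowed and not allowed food to clarify even more the restricted food to the volunteers". The caption of that list (Figure 2) adds: "The list is delivered to the volunteers to be better informed about the diet to follow during the study". Its restricted column has five food entries: pasta, breads or similar, baking products, breakfast cereals and snacks. The only restricted beverage is beer. The permitted column reads "Fruit • Vegetable • Meat • Fish • Nuts • Dairy products • Eggs", and its beverage entry is simply *Other*.

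Three further statements bear on the point:

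- The Methodology section uses the urine taken before the toxin as the check on the diet, and says that the volunteers are otherwise trusted.
- Under Problems Anticipated, volunteers restart if they are aware of a mistake in the diet.
- The Study Design section collects urine for 24 hours from the moment of administration on the morning of day 3.

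**The concern.** The study aims to describe the excretion pattern of DON and its metabolites and their absorption and excretion rates. The measured quantity is the amount in urine over the 24 hours after a known oral dose. DON from food eaten in that window cannot be told apart from DON from the bolus. It would raise the apparent recovery and distort the hourly profile. In the DON-3-glucoside period it could also pass for DON released from the glucoside.

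The diet is the main protection against this, and the investigators state that they cannot supervise it. The instructions to volunteers therefore carry much of the control. If the sheet is narrower than the rule, a cooperative volunteer may depart from the protocol diet without knowing it.

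**Working it through.** **Step 1: compare the lists item by item.** The Study Design section names 19 items. Each is set against the restricted side of Figure 2.

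| Protocol items | Counterpart on the sheet |
|---|---|
| Bread and bread-based products | Breads or similar |
| Breakfast cereals, oat meal, muesli | Breakfast cereals |
| Waffles, cakes | Baking products |
| Cereal bars, popcorn, cereal-based chips | Snacks |
| Pasta | Pasta |
| Beer | Beer |
| Wine | None; permitted under *Other* beverages |
| Maize | None; could be read as a permitted vegetable |
| Rice, polenta, pizza, tortilla, pan meal, sauce-binders | None; in neither column |

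Covered: 1 + 3 + 2 + 3 + 1 + 1 = 11. Without a clear counterpart: 1 + 1 + 6 = 8. Total: 11 + 8 = 19. The rule on possible traces is also absent from the sheet. The reading is generous where an entry can reasonably stretch. Pizza and tortilla might also be placed under "Breads or similar (small toasts, sliced bread" and so on, which would leave 6 without a counterpart.

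**Step 2: ask which safeguard would catch the intake.**

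- *Pre-dose urine.* It precedes the bolus, so it can reveal earlier intake. It says nothing about meals later on day 3, all of which fall inside the 24-hour collection. The Rationale section describes the excretion half-life of DON as short, so such intake could appear in that same window.
- *Restart rule.* It needs the volunteer to know of a mistake. Someone relying on the sheet would not.
- *Food-intake questionnaire.* It can show the missing items, but the protocol does not say that it is checked against the restricted list.
- *Four undosed controls.* They follow the same diet and can show a group background. They cannot show what one dosed volunteer ate.

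**Step 3: illustrate the size.** The documents give the dose (1 µg/kg) but no DON content of any food. Body weight (70 kg), portion (200 g) and concentration (10 to 500 µg/kg) are assumptions.

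Bolus = 1 µg/kg × 70 kg = 70 µg. Intake from food = 0.2 kg × concentration.

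| Assumed concentration (µg/kg) | Intake (µg) | Share of bolus |
|---|---|---|
| 10 | 2 | 2/70 = 3% |
| 50 | 10 | 10/70 = 14% |
| 100 | 20 | 20/70 = 29% |
| 200 | 40 | 40/70 = 57% |
| 500 | 100 | 100/70 = 143% |

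These are shares of intake. They carry over to urinary recovery only if DON from food is absorbed and excreted like the bolus and within the window. A meal late on day 3 would count for less. No corresponding figure can be given for wine.

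**The case against.** The strongest reply is that the sheet is not the whole instruction. The Methodology section tells volunteers to go three days without cereals and offers the list as further clarification. That general rule reaches rice, maize and polenta. The recommendations printed with the list suggest only cereal-free meals. The figure with the volunteer instructions is not shown in the text at hand and may say more. These points stand, and they make contamination a possibility rather than an established fact. They do not remove the conflict on wine, and a no-cereals rule does not plainly cover sauce-binders.

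A reader might infer that anyone who obeys the sheet necessarily breaks the protocol diet on all eight items. The documents do not support that. Only wine is positively permitted, and maize only on one reading. The other six items are in neither column, so the sheet is silent on them.

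A reader might also infer that all DON in urine after dosing is credited to the bolus. The protocol does not say so. It provides the controls for comparison, and they can reveal background from the shared diet. What remains is that four people cannot correct an individual's recovery.

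Finally, the percentages above might be taken as an estimate of bias. They are not: every input except the dose is assumed, and the range runs from negligible to larger than the bolus.

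**Conclusion.** The inconsistency is real. The sheet contradicts the protocol on wine and lacks a clear counterpart for 8 of 19 named items, wine included. Intake after the bolus by a volunteer relying on the sheet would escape both the pre-dose urine and the restart rule. Any resulting bias in recovery would be upward. Its size cannot be computed from the documents; the illustrative 3% to 143% of a 70 µg bolus rests on the assumed weight, portion and concentrations. Whether any volunteer actually consumed these items cannot be known from the protocol. The point is a correctable inconsistency with a possible bias of unknown size, and does not show that the data are contaminated.

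**What to change.** **For any repeat or further diet period:** reconcile the Project summary and Study Design section with Figure 2, so that the sheet carries the same restricted list as the protocol. In particular, settle the status of wine against the *Other* beverages entry and of maize against the vegetable entry. The cost is one reprinted sheet.

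**For collections already made:** this is the more useful step, because the Duration of the Project section reports sampling and laboratory analysis as finished.

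- Screen the daily food-intake questionnaires for the eight items missing from the sheet, noting whether intake fell before or after the bolus.
- Compare the findings with the background seen in the controls.
- Report a sensitivity analysis of recovery and excretion profile without the affected collections.

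The protocol already requests the questionnaires, so no new procedure is needed. The price is a little more analysis work and possibly fewer collections in the sensitivity analysis, with wider uncertainty in a study of 20 volunteers.
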